**Version history**

| Version number | Date       | Summary of changes                                                                                                                                                                                                                                                                                                                                                                                   |
|----------------|------------|------------------------------------------------------------------------------------------------------------------------------------------------------------------------------------------------------------------------------------------------------------------------------------------------------------------------------------------------------------------------------------------------------|
| 1.0            | 12.12.2023 | First version                                                                                                                                                                                                                                                                                                                                                                                        |
| 2.0            | 21.2.2024  | Because of the Request for Information by the Authority
1. An additional secondary objective 6 has been added, and accordingly, text has been revised in sections 'Introduction', 'Secondary response variables', 'Laboratory methods' and 'Data collection from registers and participants'.
2. Exclusion criteria have been added
Typographic errors have been corrected                  |
| 3.0            | 28.10.2024 | 1. Current information on the avian influenza disease, vaccinations and target groups have been updated
2. Sampling time window (visit 1) changed
3. Validation of the laboratory methods for influenza and avian influenza has been added as an exploratory objective, with additional serum samples collected for validation purposes
4. New information about the funding has been added |

**Investigator, sponsor and data controller:** Finnish Institute for Health and Welfare (THL)

## Abstract

This study was designed to be carried out in an exceptional situation where highly pathogenic avian influenza A(H5N1) virus belonging to clade 2.3.4.4b, enzootic in many parts of the world including Europe, was causing large outbreaks among farmed foxes, minks and raccoon dogs in Finland in 2023. The widespread infections observed in mammals, and especially transmission of the virus between mammals, is a significant cause of concern because of the well-recognized pandemic risk of the virus. Since the beginning of 2024, the outbreaks have been controlled in Finland, and only one A(H5N1) infected bird has been detected by October 2024. Globally, however, A(H5N1) outbreaks continue occurring, and the virus has been detected in new species of mammals, i.e cows in the USA. In Europe, 75 highly pathogenic A(H5N1) and A(H7) virus detections were reported in domestic (16) and wild (59) birds between 15 June and 20 September 2024 [1]. The risk of infection with currently circulating avian A(H5) influenza viruses of clade 2.3.4.4b has been estimated to remain low for the general public in the European Union/European Economic Area (EU/EEA), but the risk of infection is low-to-moderate for those occupationally or otherwise exposed to infected animals or contaminated environments [1].

One of the planned precaution measures is to provide avian and seasonal influenza vaccines to people at risk through direct exposure to infected animals or indirectly through handling potentially infectious material. These groups include people working in fur farms, people working with poultry, official veterinarians, laboratory workers who work with avian influenza samples, people taking part in culling and disposal of affected animals and other people at special risk of avian influenza such as bird ringers.

No vaccines are administered in this study, but the vaccines distributed in the national influenza vaccination program and in the national avian influenza vaccination campaign will be evaluated. Seasonal influenza vaccination has been recommended to fur farm workers and other risk groups (from 12 September 2023 on) as part of the national vaccination program since September 2023. Based on previously reported immunological research results, it is possible to achieve partial cross-protection with seasonal influenza vaccines, although there is little evidence of its clinical significance in humans. The seasonal influenza vaccine is also considered to be beneficial by reducing the risk of co-infection with seasonal and avian influenza viruses and thereby minimizing the risk of reassortment. The updated avian influenza virus vaccine customized to match the clade 2.3.4.4b virus has been offered to the same target groups since the vaccine received market authorization and became available in June 2024.

For this clinical trial, we aim to recruit 300 subjects for assessment of avian influenza vaccine induced humoral immune responses in serum samples. From a smaller number of subjects, we will also evaluate vaccine induced mucosal immunity (salivary samples) and cell-mediated immunity from blood cell samples. The samples are to be collected before avian influenza vaccination, 3 weeks after the administration of each of the two vaccine doses and 6 and 12 months after administration of the last vaccine dose. Yearly follow-up samples and samples after possible vaccine booster doses can be collected up to 10 years.

The main aim of this study is to evaluate the immune response produced by the avian influenza vaccine, customized specifically against the H5N1 clade 2.3.4.4b. We will also evaluate the immune responses produced by the avian influenza vaccine against different H5N1 clades that have been circulating in Europe before 2023 and which will be circulating during the follow-up.

In addition, we will assess potential cross-recognition of avian influenza viruses by samples collected from subjects immunized with seasonal influenza vaccines. We will measure the immunity produced

by seasonal influenza vaccinations against different H5N1 clade viruses from serum samples collected from healthcare personnel belonging to the target group of the seasonal influenza vaccine as part of a separate clinical trial, where pre- and post-vaccination samples have been collected during each epidemic season since 2017 ("Immune Responses to influenza vaccinations and viruses among health care personnel", ClinicalTrials.gov Identifier: NCT03323112).

The distribution of seasonal influenza vaccines took place from October through November 2023, which was 1-3 months before the expected start of the distribution of avian influenza vaccines. In reality, due to delays in the licensure process, the avian influenza vaccination started only in July 2024. The avian influenza vaccine is given as a series of two doses. We will also evaluate whether receiving the seasonal influenza vaccine prior to the avian influenza vaccine, or the length of the interval between the vaccine doses influence vaccine-induced immune responses.

A small target group of laboratory personnel has previously been given avian influenza vaccines in 2009 and 2011 in Finland. Some of the individuals who previously received the vaccine are also included in the target group of the avian influenza vaccine that is now being distributed. One of the goals of this study is also to evaluate vaccine-induced responses against different virus lineages in persons who have previously received the avian influenza vaccine. We will also evaluate the cross-reactivity of antibodies, especially against the H5N1 2.3.4.4b clade, produced by the previous avian influenza vaccines from samples collected from these subjects previously, and at baseline for the current study.

For the analysis of the serum samples, we will use an in-house microneutralization test that we have developed and used in previous studies of avian influenza vaccine responses [5] and, depending on the virus clade under investigation, also the hemagglutination-inhibition (HI) assay. We will isolate peripheral blood monocytes and study vaccine induced cell-mediated immunity by analyzing the activation and persistence of avian influenza antigen induced T cell responses. Cross-recognition of T cell responses against different clade avian influenza viruses is also analyzed.

Based on the research data collected during this study, it is possible to estimate the immunity induced by the avian influenza vaccine and thus the possible level of protection in the target groups of the vaccine. Specifically, we will be able to assess the level of seroprotection and cross-protection that can be achieved with the customised vaccine product, how immunity is maintained, and on the other hand, how previous administered seasonal influenza vaccines affect the immune response. In addition, the research will be able to monitor the ability of possible new virus lineages to evade the seroprotection achieved by vaccination.

## Introduction

Highly pathogenic avian influenza A(H5N1) clade 2.3.4.4b viruses have been circulating abundantly in Europe among wild and reared bird populations since 2020. As a consequence of the virus spreading from waterfowl to shorebirds, most significantly gulls in 2023, mass deaths of wild birds due to avian influenza were observed for the first time in Finland in the spring of 2023. Shortly after, infections started to spread from the wild bird populations to farmed fur animals [2]. In July 2023, highly pathogenic influenza A(H5N1) was detected in silver and blue foxes, American minks and raccoon dogs and confirmed by RT-PCR on 27 fur farms in Finland [3]. Outbreaks were detected by either RT-PCR or serology on a total of 70 farms in Finland in 2023.i). Since 2024, only one A(H5N1) virus detection in a wild bird was made in Finland. Globally, highly pathogenic avian influenza detections are being made, as well as observations of virus transmission in new mammalian species, i.e. cows in the USA.

All currently circulating highly pathogenic avian H5N1 viruses are foremost avian pathogens with a poor ability to infect and spread among humans. Human-to-human transmission is extremely rare. During the years 2021-2024, the A(H5N1) clade 2.3.4.4b virus has reportedly caused a small number of human infections globally. Although a relatively large number of people have been exposed to infected animals during the outbreak among farmed fur animals, so far, not a single human infection has been detected. In the USA, highly pathogenic influenza in cows was first reported on March 23, 2024. As of today (October 2024) per information from the USA Centers for Disease Control and Prevention, the virus has been detected in total 304 herds, in 14 states.

Previous pandemic influenza viruses have been characterized by their ability to transmit easily from one human to another and to evade prior population immunity sufficiently to allow sustained transmission. Although the population immunity to avian influenza viruses is low or non-existing, there are several factors that have prevented the transmission of the virus between humans. Most importantly, the surface glycoproteins of avian influenza viruses have a low affinity to the cell receptors in the upper respiratory tract of humans. Due to the intrinsic nature of influenza viruses mutating in response to environmental changes, there is a risk of mammalian adaptation of avian influenza viruses during replication in mammalian hosts. Whole-genome sequencing and genomic analyses of viruses isolated during the fur-farm outbreak have been studied to track changes in the virus genomes, with a focus on mutations that may have indications on the zoonotic potential of the virus. The analyses revealed several virus isolates with mutations indicative of an early mammalian adaptation. Most notably, mutations in the polymerase gene PB2 allowing for more efficient replication in the upper respiratory epithelia of mammals, seem to have evolved independently on a number of affected farms. The accumulation of such mutations among circulating avian influenza viruses may increase the pandemic potential of the virus by improving its ability to transmit and cause disease in humans. Although human transmission still appears to be very rare, spill-over events from the wild bird population to mammals are becoming more frequent, and the risk of sporadic infections in humans cannot be neglected. Altogether, sporadic and small outbreaks of avian influenza infections have been seen in more than 40 mammalian species.

Virus circulation at the human-animal interface, as is demonstrated by the ongoing fur farm outbreaks, further increases the risk of emergence of a pandemic avian influenza virus. Due to Finland's exceptional epidemic situation and the increased risk of a pandemic, Ministry of Social Affairs and Health (STM) has made a decision to participate in the EU's joint vaccine procurement. AFLUNOV, manufactured by Seqirus, has been on the market since 2010, contains the H5N1 A/turkey/Turkey/1/2005 virus, which is a virus of the development line 2.2.1 [6]. Antigenically and genetically, the older vaccine virus differs from the currently circulating development line 2.3.4.4b H5 viruses, which is why the manufacturer is currently customizing the vaccine to the A/Astrakhan/3212/2020 (H5N8) strain, in which the H5 protein is almost identical to the H5 protein of circulating avian strains found in Finland. It is expected that a tailored vaccine would provide moderate to good protection against the circulating clade 2.3.4.4b viruses through cross-reactivity and protection. Cross-protection can be based on both antibody-mediated and cell-mediated immunity, which recognizes common structures of the vaccine virus and circulating viruses. However, it must be noted that influenza viruses are constantly changing as the virus multiplies, but also through reorganization of the virus's inheritance, which may result in a virus capable of circumventing the protection provided by the vaccine.

The vaccines were expected to be in use in the beginning of 2024, but due to delays in the registration process, vaccination was initiated only in June 2024. The target groups to be vaccinated were decided based on an updated risk assessment. The target groups include people working in fur farms and poultry industry, official veterinarians and laboratory workers or people working in the collection or analysis of bird influenza samples. In addition, the vaccine is offered to other persons

over the age of 18 who are at special risk, such as bird ringers. The vaccine is given in a series of two doses, where the second dose is given three weeks or later after the first dose.

There is no approved correlate of immunity to protection against infections due to influenza A (H5N1), but it is widely believed that the protection against influenza can be conferred by serum hemagglutinin (HA) antibodies. In the licensing of pandemic influenza vaccines, assessment of seroconversion and seroprotection is a critical requirement.

In the assessment of influenza vaccines, two key immunological parameters are considered: seroconversion and seroprotection.

## Seroconversion

Definition: The acquisition of detectable virus-specific antibodies in response to vaccination

Measurement: Quantification of anti-HA antibodies pre- and post-vaccination to observe an increase

Significance: The observation of seroconversion indicates that the vaccine has induced a significant increase in virus-specific antibodies that can be measured by several laboratory methods.

## Seroprotection

Definition: The presence of a sufficiently high antiviral antibody levels expected to be associated with protection against a disease.

Measurement: Evaluation of anti-HA antibody levels post-vaccination to determine if they reach a protective threshold.

Significance: Seroprotection is expected if sufficiently high levels of antiviral antibodies are found in the sera of vaccinated individuals that likely gives protection against influenza disease. *Seroprotection rate* refers to the proportion of subjects in whom the level of anti-HA (or neutralizing) antibodies exceeds the value considered to be the limit of a significant level in terms of protection, e.g. the HI titer measured with the hemagglutination inhibition test (HI test)  $\geq 1:40$ . In addition to this, it is possible to evaluate the seroprotection as an increase in antibody concentration when the pre-vaccination sample is seropositive (e.g. HI titer  $>10$ ) and to estimate in how many of the study subjects the antibody (Ab) increase exceeds the factor considered as a critical response, a fourfold increase in the titer. In other words, if the pre-vaccination serum is negative, the postvaccination serum titer must be  $\geq 40$ ; if the pre-vaccination serum is positive, at least a fourfold increase in antibody titer is required.

According to the summary of product characteristics (SPC) of the currently marketed vaccine [3], based on the antibody responses elicited by the A/turkey/Turkey/1/2005 vaccine strain after two doses of AFLUNOV, a protective response may not be elicited in all recipients of the vaccine. According to previous research results presented in the SPC, the seroprotection rate against the homologous A/Vietnam/1194/2004 strain measured by the microneutralization (MN) test in adults aged 18-60 who received two doses of the vaccine was 67% (95% confidence interval 60–74) to 85% (78–90) and the seroconversion rate was 65% (58–72) to 83% (77–89). The seroprotection rate against the homologous A/turkey/Turkey/1/2005 strain measured with the MN test was 85% (79–90) and the seroconversion rate was 93% (89–96). Some cross-reactive immunity has been observed against H5N1 viruses from other clades. However, it is not known to what extent protection can be achieved against different H5N1 clade viruses. There is no immunological research data yet available for the avian influenza vaccine tailored against the A/Astrakhan/3212/2020 (H5N8) strain.

In a previously published study, it was found that the seasonal influenza vaccine produced neutralizing antibodies also against H5N1 viruses in a large proportion of the subjects, indicating the

existence of an antibody-dependent cross-reactivity [7]. At one month after seasonal influenza vaccination, 28/38 (74%) showed a >4-fold increase of neutralizing antibody titer measured with neutralization test, and 13/38 serum samples (34%) showed a 20-fold increase of neutralizing Abs against influenza H5N1. HI titers against H5N1 remained at undetectable levels after seasonal vaccination in 13/38 (34.2%) of donors [7]. Also, H5N1 virus-specific CD4 T cell responses (in small frequency) were detected in several persons at baseline, and vaccination with a seasonal influenza enhanced the frequency of H5N1 specific CD4 T cells [7]. At 1 month after seasonal influenza vaccination influenza H5N1 specific CD4 response was detectable in 41.6% of study participants. Another study reported that vaccination with seasonal influenza vaccine provided a partial protection against a lethal H5N1 challenge in mice, and it was suggested that seasonal influenza vaccination could be used as an interim measure to decrease morbidity and mortality from H5N1 prior to the availability of a specific vaccine [8]. Mouse experiments have also shown that non-neutralizing antibodies against HA epitopes produced by multiple immunizations with seasonal influenza vaccines that are at least in part directed against conserved HA epitopes, mediated protection from challenge with H5N1 even in the absence of detectable neutralizing antibodies against the H5N1 virus [9]. Based on these findings, it is possible that partial cross-reactivity, potentially even some cross-protection may be achieved with the seasonal influenza vaccine through both neutralizing and non-neutralizing antibodies, and T-cell-mediated immunity, at least in some of the vaccinated. Since the concentration of serum antibodies remains at its highest for about three months after vaccination, and since the proportion of potentially cross-reacting antibodies is relatively small, it would be expected that the effect (cross-reactivity and possible cross-protection) may last a relatively shorter time after vaccination.

The samples collected in this study are unique, because they represent immune responses against the first avian vaccinations and in a situation, where no human spread of the avian influenza has happened so far. Previous infection and vaccination history may have unknown effects on responses to later administered vaccines, such as the avian influenza vaccine under investigation in this study. Studying innate immune responses can help to better understand the immune responses triggered by vaccination that influence the development of acquired immunity. Thus, it is extremely important that a H5N1 virus-specific avian influenza vaccines are used to protect fur farm workers and other people potentially exposed to avian influenza viruses. It is also very important that when the H5N1 vaccination campaign starts in Finland we collect information on the immunogenicity, cross-reactive immune responses and the duration and specificity of humoral and cell-mediated immunity induced by avian and seasonal influenza vaccines. The data obtained in our project has huge national and international needs and interests and the information is essential for global preparedness against influenza pandemics.

## Objectives

The main objective of this study is to evaluate the humoral and cell-mediated immune responses induced by the customized avian influenza vaccine, specifically against the H5N1 2.3.4.4b clade.

## Secondary objectives

To evaluate

1. humoral immune responses produced by the avian influenza vaccine against different H5N1 development lineages (clades) that have occurred before 2023, or that are identified to occur during the study

2. cellular immune responses induced by the customized avian influenza vaccine, against different H5N1 clades
3. the effects of prior seasonal influenza vaccinations on the immune responses induced by the avian influenza vaccine
4. humoral immunity produced by seasonal influenza vaccinations against different H5N1 lineages evaluated from samples collected from healthcare personnel belonging to the target group of the seasonal influenza vaccine (“Immune responses to influenza vaccinations and viruses among health care personnel”, ClinicalTrials.gov Identifier: NCT03323112)
5. humoral and cellular immune responses induced by the H5N1 2.3.4.4b customized vaccine in subjects who have previously received avian influenza vaccines
6. humoral and cellular immune responses induced by other respiratory or non-respiratory pathogens and vaccines against them, and their potential association with immune responses induced by seasonal and avian influenza vaccines or viruses

### Exploratory objective

Development of laboratory methods for influenza and avian influenza

**Primary outcome measure:** Seroconversion proportion in all study subjects 3 weeks after the second dose given at least 21 days after the first dose, as assessed by the microneutralization test.

### Study hypothesis

It is expected that a two-dose avian influenza vaccination schedule will induce **seroprotection** in at least 70% of the vaccinees (the lower bound of the two-sided 95% CI for the percent of subjects achieving seroconversion meets or exceeds 70%). The criterion for seroprotection is titer value  $\geq 80$  as analyzed by microneutralization test (MNT).

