### Secondary response variables:

- Rate of **seroconversion** defined as the percentage of subjects with either a pre-vaccination MNT titer  $< 1:10$  and a post vaccination MNT titer  $\geq 1:80$  or a pre-vaccination MNT titer  $\geq 1:10$  and a minimum four-fold rise in post-vaccination HI antibody titer.
- Geometric mean titers at pre- and post-vaccination.
- Detectable increase in T cell (CD4+ and CD8+) responses against H5N1 virus specific antigens in avian influenza virus vaccinated individuals.
- Geometric mean antibody titers and detectable T responses against other pathogens and/or vaccines of interest in the target group of the avian influenza virus vaccine.

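### The 70% hypothesis is stated for seroprotection but judged by the confidence interval for seroconversion, which the protocol lists as both the primary outcome and a secondary variable

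*Protocol*

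**What the plan says.** Five places in the protocol bear on this.

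- **Primary outcome measure** (printed under Exploratory objective): "Seroconversion proportion in all study subjects 3 weeks after the second dose given at least 21 days after the first dose", assessed by MNT.
- **Study hypothesis:** seroprotection is expected "in at least 70% of the vaccinees". The bracketed decision rule is that "the lower bound of the two-sided 95% CI for the percent of subjects achieving seroconversion meets or exceeds 70" per cent. The paragraph then adds: "The criterion for seroprotection is titer value" at or above 80 by MNT.
- **Secondary response variables:** the first item is the rate of seroconversion, "defined as the percentage of subjects with either a pre-vaccination MNT titer" below 1:10 and a post-vaccination MNT titer of at least 1:80, or a baseline MNT titer of at least 1:10 "and a minimum four-fold rise in post-vaccination HI antibody titer". This is the only operational definition of seroconversion in the protocol. Seroprotection is not in the list.
- **Sample size:** 288 subjects (target 300), from an assumed seroconversion rate of 75%. No seroprotection rate is assumed.
- **Introduction:** seroconversion is described as "The acquisition of detectable virus-specific antibodies in response to vaccination". Under Seroprotection, the text says that "it is possible to evaluate the seroprotection as an increase in antibody concentration when the pre-vaccination sample is seropositive", so a fold-rise rule also appears under the name of seroprotection.

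**The concern.** The hypothesis names one endpoint and its decision rule uses another. Followed literally, the study would announce that at least 70% of vaccinees are seroprotected on the strength of an interval for seroconversion. The protocol says under Reporting of the results that the findings will inform vaccination policy, and the two statements mean different things there: one concerns the titer reached, the other the change from baseline.

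Listing seroconversion as both primary and secondary, with its definition only in the secondary list, leaves a reader unsure which result answers the hypothesis.

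The choice also has a practical side. Under the alternative recruitment route, people who have already been vaccinated would have no pre-vaccination sample from this study. A titer threshold could be assessed for them, but a change from baseline could not.

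**Working it through.** **1. The planned figure.** Inputs from Sample size: Z = 1.96 (95% confidence), p = 0.75, E = 0.05.

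n = Z²p(1 − p)/E² = 3.8416 × 0.1875 / 0.0025 = 288.1. The stated 288 reproduces, and it belongs to seroconversion.

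**2. How much room the rule leaves.** With n = 300, a lower 95% limit of at least 70% needs 225 responders (Wald) or 226 (Wilson or Clopper-Pearson), i.e. 75.0% or 75.3%. The planning rate of 75% therefore sits on the pass mark, and a gap of a few points between endpoints can change the verdict.

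**3. Where the endpoints agree and differ.** Seroprotection is taken from Study hypothesis, seroconversion from Secondary response variables.

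- Baseline MNT below 1:10: both require a post-vaccination MNT titer of at least 80, so they are the same event.
- Baseline MNT 1:10 or higher: seroprotection still asks for a titer of at least 80, while seroconversion asks for a four-fold rise. A subject who starts at 80 or above and stays there without a four-fold rise is seroprotected but not seroconverted, whichever assay measures the rise.

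**4. Illustration.** The protocol gives no baseline-positive share b, so all rates here are assumptions. Let q be the proportion of baseline-negatives reaching 80. Among baseline-positives, let s be the proportion at 80 or above and c the proportion with a four-fold rise.

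- Seroprotection = (1 − b)q + bs
- Seroconversion = (1 − b)q + bc
- Gap = b(s − c)

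With q = 0.77, s = 0.95, c = 0.50, n = 300, counts rounded to whole subjects, and Wald lower limit = p − 1.96√(p(1 − p)/n):

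| b | Seroprotection (count; lower limit) | Seroconversion (count; lower limit) | Gap |
|---|---|---|---|
| 5% | 77.9% (234; 73.3%) | 75.65% (227; 70.8%) | 2.25 points |
| 10% | 78.8% (236; 74.0%) | 74.3% (223; 69.4%) | 4.5 points |
| 20% | 80.6% (242; 76.2%) | 71.6% (215; 66.6%) | 9.0 points |

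Both endpoints pass at 5%. At 10% and 20% seroprotection passes and seroconversion fails. Against the pass marks in step 2, no verdict in the table depends on the interval method.

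**5. Sensitivity to the assumptions.**

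- With c = 0.70 and the rest unchanged, the seroconversion lower limits are 71.9%, 71.5% and 70.8%, so both endpoints pass at all three shares.
- With q = 0.75 and c = 0.40, the seroprotection lower limits are 71.2%, 72.2% and 74.4% and the seroconversion limits 68.3%, 66.6% and 62.7%, so the verdicts split at all three shares.

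Opposite verdicts from the same data are possible, but not certain.

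**The case against.** The strongest reply is that this is a slip of one word. The labelled primary outcome, the interval in the decision rule and the sample size all use seroconversion, and the Introduction lets the two terms overlap. The hypothesis is phrased as an expectation, in an uncontrolled, low-intervention phase IV study. Much of this stands: seroconversion is probably the intended endpoint. But the hypothesis paragraph names seroprotection and gives it its own fixed titer threshold, which is not the fold-rise rule of the Introduction, and the secondary list then includes seroconversion. Nor is this a detail left to an analysis plan, because the protocol fixes both statements and they conflict.

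Four stronger readings are tempting, and the documents do not support them.

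- *A reader might infer that the study has no identifiable primary endpoint, or may pick one after seeing the data.* The primary outcome measure names exactly one.
- *A reader might infer that an MNT rise from 10 to 40 is seroconversion without seroprotection.* As written, the four-fold rise for baseline-positive subjects is in HI titer, so that MNT rise alone does not meet the definition.
- *A reader might size the gap from the product-information rates in the Introduction* (seroprotection 85% against seroconversion 93% for one strain; 67% against 65% and 85% against 83% for another). These concern older strains, and the cut-offs behind them are not given. The two-point differences lie well inside overlapping intervals. Under this protocol's definitions, an eight-point excess of seroconversion would need at least 8% of all subjects to be baseline-positive, to seroconvert and still to remain below 80.
- *A reader might assume a large baseline-positive share.* Cohort 2 had earlier H5N1 vaccines, and the Introduction cites a more than four-fold neutralizing rise against H5N1 in 28 of 38 people after seasonal vaccination. But it also describes population immunity as low or absent, and the Abstract calls the group previously vaccinated against avian influenza small.

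**Conclusion.** The point holds as an internal contradiction. The 70% hypothesis is stated for seroprotection and decided on seroconversion, seroconversion is both primary and secondary, and seroprotection is in neither outcome list. Because the endpoints can differ when baseline MNT is 1:10 or higher, the interval named in the rule cannot support the claim made in the hypothesis.

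The size of the gap cannot be established from the protocol. It is the baseline-positive share times the net discordance among those subjects, and neither is given. Under the main assumed rates it runs from 2.25 to 9.0 points for shares of 5% to 20%, and the verdicts part at 10% and 20%. Under the other assumed rates tried, they part at every share or at none.

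**What to change.** Preferred change, which follows the majority of the protocol's own statements:

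1. Make seroconversion by MNT at visit 3 the single primary endpoint.
2. Restate the hypothesis so that claim and rule match: the two-sided 95% interval for the seroconversion proportion has a lower limit of 70% or more.
3. Move the operational definition of seroconversion from Secondary response variables to the primary outcome measure. Deleting it without moving it would leave the primary endpoint undefined. In moving it, express the four-fold rise in MNT titer, to agree with the assay that the primary outcome names.
4. List seroprotection (MNT titer of at least 80) as a secondary variable with its own 95% interval.

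If the 70% bar was meant for seroprotection, name that as primary instead, and change the primary outcome, Study hypothesis, Secondary response variables and Sample size together, with an assumed seroprotection rate in the last.

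Either way the cost is a protocol wording amendment, with no new data. Under the preferred change the sample size calculation stays at 288. Under the alternative it has to be redone with the assumed seroprotection rate.
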